## Data Collection

Primary and secondary outcomes: Primary outcomes include self-efficacy, self-care behaviour and knowledge. Secondary outcome is readmission rate within 28 days.

Baseline (Time 1): When patients' physical condition is stable they will be invited by a Research Assistant (RA) to participate in the study. Following explanation of the study, demographic and baseline data will be collected for those giving informed consent.

One month follow-up (Time 2): A questionnaire will be posted to participants at their discharge location, after which the RA will telephone the participant and collect data over the phone. Posting the questionnaire first will facilitate data collection in the telephone interview. This method has been used previously by a research team member [24], resulting in a high response rate (84%).

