### Hypotheses

• Anticipated outcomes for the intervention group when compared to the control group receiving usual care will include:

• Higher self-management practice scores;

• Higher self-efficacy levels;

• Higher knowledge scores.

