### Phase 1: Development of the CDSMP

The intervention utilised in this project will be based on the Cardiac Diabetes Self Management Program developed in earlier research by the first two authors [12]. It will be modified according to feedback from its initial trial, which included suggestions for adding a multimedia component; this will take the form of a DVD. The DVD will be provided to participants in the intervention group to assist them to apply strategies from the self-efficacy model; it will take the form of narrative "real-life" stories of people managing both diabetes and cardiac conditions. A further addition to the program will be the use of peers to provide follow-up support to participants.

The CDSMP program consists of three face-to-face sessions and telephone and text-messaging follow-up. The face-to-face sessions will be provided by a trained Research Nurse, and be conducted while the patients are in CCU and continue as the patient makes the transition home after discharge. The participants will be telephoned 1 week after discharge home and 2 text-messages will be sent a week after telephone follow up. These will be conducted by the trained 'peers'.

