### Phase 3: Intervention

Control group (group 1): Participants will receive usual care, which consists of education provided in the CCU and referral as necessary to the diabetes educator.

Intervention group (group 2): Participants will receive usual care and a combination of CDSMP sessions in the CCU, plus peer telephone and text follow-ups.

The CDSMP is designed to be administered on a one-to-one basis and to commence in CCU by staff members, then be followed up by trained peers via a telephone call one week after discharge and text message reminders from peers in weeks three and four. If a patient is transferred to a ward before completing the program, the hospital-based section of the CDSMP will be continued on the ward by the trained research nurse.

As part of the program, the DVD based on incorporating stories from a range of case studies is developed and will be provided to participants in the intervention group to assist them with the application of strategies from the Self-Efficacy Model.

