#### Knowledge

Data will be collected at Time 1 and Time 2, and will be measured using Diabetes Knowledge Questions (DKQ) [27]. The DKQ measures patients' knowledge of diabetes and cardiac conditions. Each item with a correct answer scores one point; score ranges are therefore 0 to 8. Cronbach alpha for DKQ is 0.7, indicating good internal consistency [27]. In addition, this scale is brief and unlikely to cause a 'response burden'; particularly as patients who have diabetes and have had a cardiac condition may become tired answering questions. Permission to use this tool has been granted.

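### The Time 2 questionnaire is posted home before the telephone interview, so the right/wrong knowledge test, a primary outcome, can be answered with advance sight of its items

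*Protocol article*

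**What the plan says.** The Data Collection section of the protocol article gives one route for patient-reported data at one month: "A questionnaire will be posted to participants at their discharge location, after which the RA will telephone the participant and collect data over the phone". The reason given is practical: "Posting the questionnaire first will facilitate data collection in the telephone interview". A response rate of 84% in earlier use is cited in support.

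The same section lists the endpoints: "Primary outcomes include self-efficacy, self-care behaviour and knowledge". The Knowledge section makes the DKQ a measure at both time points and describes the scoring: "Each item with a correct answer scores one point; score ranges are therefore 0 to 8". The Hypotheses section predicts, for the intervention group against usual care, "Higher knowledge scores".

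On materials, the Phase 1 section states: "The DVD will be provided to participants in the intervention group to assist them to apply strategies from the self-efficacy model". The same section describes the DVD as narrative stories. Under Phase 3, controls receive usual care, meaning education in the coronary care unit and referral to the diabetes educator where needed. Intervention participants also receive a peer telephone call one week after discharge and peer text reminders in weeks three and four.

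At Time 1, the Data Collection and Procedure sections have the research assistant (RA) collect baseline data after consent and before allocation. No posting is mentioned.

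**The concern.** Posting a questionnaire ahead of a telephone interview suits self-ratings. The SDSCA and the DMSES have no correct answers, so seeing the items early gives nobody an advantage. A knowledge test is different. Once the items are in the home for an unstated time, the score mixes what the person knows with what the person found out for the occasion.

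Two comparisons are exposed. The first is the change from Time 1 to Time 2 within each group, which the Data Analysis section tests with the Wilcoxon signed rank test: advance sight is described at Time 2 only. The second is the comparison between arms. If intervention participants find answers more readily because they hold programme materials, the error runs in the same direction as the hypothesis, and the planned tests cannot separate it from learning.

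The Limitations section says the pilot is to guide the power analysis of a larger study, so an inflated knowledge effect would carry forward.

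**Working it through.** **Is the DKQ in the mailing?** The article does not list the posted instruments. It describes one Time 2 questionnaire and one way of collecting the answers, makes the DKQ a Time 2 measure, and exempts nothing. Inclusion is therefore the natural reading, though not an explicit statement.

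**Illustration.** The plan gives no figure to reproduce here, and every look-up rate below is an assumption. From the document: DKQ range 0 to 8, 30 patients (taken as 15 per arm), Mann-Whitney U test, significance at 0.05 (two-sided assumed). Assumed: both arms truly know 60% of items on average (individual probability roughly normal, SD 0.12); a fraction f of an arm looks answers up; each missed item is then corrected with probability r.

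The expected number of missed items is 8 × (1 − 0.60) = 3.2. The expected rise in an arm's mean score is f × r × 3.2, with no true effect. If only the intervention arm looks answers up, that rise is also the spurious difference between arms:

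| f | r | Rise in mean (points) | False-positive rate |
|---|---|---|---|
| 0 | – | 0 | about 4.5% |
| 0.25 | 0.5 | 0.25 × 0.5 × 3.2 = 0.40 | about 9% |
| 0.25 | 0.8 | 0.25 × 0.8 × 3.2 = 0.64 | about 16% |
| 0.50 | 0.5 | 0.50 × 0.5 × 3.2 = 0.80 | about 25% |
| 0.50 | 0.8 | 0.50 × 0.8 × 3.2 = 1.28 | about 50% |

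The rates come from simulation (6,000 replicates). Three readings follow.

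- *Equal look-up in both arms.* The spurious difference is zero and the false-positive rate stays near 5%. The Time 1 to Time 2 change is still inflated by 0.40 to 1.28 points in each arm: a true mean of 0.60 × 8 = 4.8 would be recorded as 5.20 to 6.08 on a scale that stops at 8.
- *Controls look up at half the intervention rate.* The difference halves to 0.20 to 0.64 points, and the false-positive rate is about 6% to 15%.
- *Only the intervention arm looks up.* This is the table: 9% to 50%.

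**Sensitivity to the score model.** A second simulation used beta-binomial scores with a mean of 50% or 70% correct, 12 or 15 per arm, and look-up applied to each unknown item. With no look-up or equal look-up, the false-positive rate was 3.6% to 5.0%. With 25% of unknown items looked up in the intervention arm and none in controls it was 10% to 29%; with 50% against 25%, 15% to 36%; with 50% against none, 38% to 80%. The pattern is the same, but the level depends strongly on the assumed rates.

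**The case against.** The strongest reply is that the article shows an opportunity and not a differential bias. The only item it says intervention participants are given is the DVD. That consists of stories meant to help people apply self-efficacy strategies, and nothing shows that it answers any DKQ item. The other programme materials are mentioned without saying what participants keep at home. Peer contact is one call at week one and outgoing texts later; no passage says participants may put questions to peers. Controls have their own education and can ask other people or use other sources. All of this stands. A reader might infer that the test is open-book for the intervention arm alone, or that a false-positive rate of up to 50% is to be expected. The document supports neither: both arms have advance sight, and the upper range requires that no control looks anything up.

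A reader might also infer that the knowledge outcome is invalid. That goes too far. The article sets no closed-book condition, and how often anyone would look answers up is unknown.

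It can further be said that a condensed article leaves such operational detail to the full protocol, that this is a pilot with feasibility aims, and that posting first is a deliberate choice to protect response in a sample of 30. The first is fair so far as the contents of the mailing go, but the article does fix the sequence of posting and calling. The second limits the consequence. The third does not require the DKQ to be posted along with the other scales.

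Finally, everyone has met the items at Time 1 and could look them up during the month. That also stands, and withholding the items at Time 2 does not remove it.

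**Conclusion.** The concern holds as a weakness in how one primary outcome is measured. Followed as written, and on the natural reading that the DKQ is in the mailing, the plan gives unsupervised advance sight of a scored knowledge test at Time 2, with nothing similar described at Time 1. The within-group change can therefore be inflated in both arms, by 0.40 to 1.28 points of 8 under the assumed rates.

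Bias between arms is possible and would favour the hypothesis, but its size cannot be established from the document. It rests wholly on how much more the intervention arm looks answers up, and the ranges above only illustrate that dependence. Self-efficacy and self-care behaviour are unaffected, because they are self-ratings. Confidence is moderate.

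**What to change.** In the Data Collection section, state that only the SDSCA and the DMSES are posted. Keep the eight DKQ items out of the mailing. Have the RA ask them first in the Time 2 call, from a fixed script with no prompting, and ask participants in both arms to answer unaided. If the DKQ is already withheld, one sentence saying so settles the point.

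The cost is a few more minutes on a call already planned, and items heard rather than read, which matters because the Knowledge section raises fatigue. Asking right/wrong items by voice also opens a route for prompting. The Procedure section says the RA assisting with data analysis is not blinded, and the article does not say whether the same person makes the calls; the fixed script limits that risk. Posting the self-rated scales keeps the practical benefit for which the mailing was chosen. The change has to be made before Time 2 data are collected.

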### Measures

Data will be collected on primary outcomes of this study: self-management practice, self-efficacy, knowledge and secondary outcome: readmission rates.

#### Self-management practice

Data will be collected at Time 1 and Time 2, and will be measured using the Summary of Diabetes Self-Care Activities (SDSCA) [25]. The SDSCA comprises 11 items that measure patients' adherence to self-management activities such as diet, exercise, blood glucose testing, foot care, and smoking status. The respondents will be asked to rate each item using 0-7 scale, with 7 indicating most adherence to each aspect, and 0 for non-compliance. Permission to use this tool has been granted by the authors.

#### Self-efficacy

Data will be collected at Time 1 and Time 2, and will be measured using the Diabetes Management Self-Efficacy Scale (DMSES) (Australian-English version) [26]. The DMSES comprises 20 items that measure patients' confidence levels (self-efficacy) in managing their diabetes. The respondents will be asked to rate each item using 0-10 scale, with 10 indicating the highest confidence level, and 0 the lowest. This scale is designed to measure the self-efficacy levels of patients with type 2 diabetes. A high internal consistency was demonstrated by the Cronbach alpha coefficient of 0.9. Face validity was established through consultation with diabetes educators and patients with type 2 diabetes, and convergent validity was demonstrated by the significant correlations between DMSES and the General Self-Efficacy Scale (GSE). Permission to use this tool has been granted.

#### Knowledge

Data will be collected at Time 1 and Time 2, and will be measured using Diabetes Knowledge Questions (DKQ) [27]. The DKQ measures patients' knowledge of diabetes and cardiac conditions. Each item with a correct answer scores one point; score ranges are therefore 0 to 8. Cronbach alpha for DKQ is 0.7, indicating good internal consistency [27]. In addition, this scale is brief and unlikely to cause a 'response burden'; particularly as patients who have diabetes and have had a cardiac condition may become tired answering questions. Permission to use this tool has been granted.

#### Readmission rate

Readmission rate will be collected at Time 2, and will be ascertained from hospital records.

### Procedure

The nominated RA will liaise with the Nurse Unit Manager (NUM) of the CCU, to obtain a list of eligible participants from the CCU Admission Book. The RA will then approach the potential participants for their informed consent and to collect baseline data. After baseline data is collected, a computer-generated list of random numbers produced by the researcher will then be used to randomly assign participants to either the control group or the intervention group (See Figure 1: Overview of data collection). Patients are blinded to receive either usual care or usual care and CDSMP, however the RA who assisting with data analysis is not blinded.

**Figure 1 F1:**
[figure not shown]
**Overview of Data Collection**.

Control group (group 1): Participants will receive usual care, which consists of education provided in the CCU and referral as necessary to the diabetes educator.

Intervention group (group 2): Participants will receive usual care and a combination of CDSMP sessions in the CCU, plus peer telephone and text follow-ups. The CDSMP was designed to be administered on a one-to-one basis and to commence in CCU by staff members, then be followed up by trained peers via a telephone call one week after discharge and text message reminders from peers in weeks three and four. If a patient is transferred to a ward before completing the program, the hospital-based section of the CDSMP will be continued on the ward by the trained research nurse.

As part of the program, the DVD based on incorporating stories from a range of case studies is developed and will be provided to participants in the intervention group to assist them with the application of strategies from the Self-Efficacy Model.

## Data Analysis

Prior to undertaking statistical tests, the homogeneity of the sample will be examined. Due to small samples size; non-parametric statistical tests will be used to determine the relationships and differences between disease and demographic variables: Chi-square for categorical variables and Mann-Whitney U test for continuous variables. The Wilcoxon Signed Rank test will be used to determine whether any changes in outcome variables occurred within and between groups over time. Mann-Whitney U test will be used to confirm whether there is an interaction between time and group. All analyses will be conducted using SPSS version 18 with a pre-defined level of statistical significance at p < 0.05.

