## Methods/Design

The pilot study using randomised controlled trial design (parallel-group trial) within the participants' usual health care environment will be conducted in three distinct but overlapping phases: (1) development of the training package including the CDSMP materials and Digital Video Disk (DVD), (2) peer selection and training, and (3) intervention phase. These will each be described below.

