## Participants

### Sample size

A total of 30 patients for 2 groups will be required. This sample size of 10-15 per group is suggested by Hertzog (2008) [19]. This number is calculated with an alpha of 0.05 and power of 0.9, thus 10 patients per group will be required to detect any statistical differences. Allowing 20% attrition rate, 13 patients per group will be required. Thus with an alpha of 0.05 and power of 0.9, 8 patients per group was required to detect any statistical differences.

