### Randomisation

Simple randomisation using a randomisation table (computerised sequence generation) will be used. Allocation will be concealed by using sealed, numbered, opaque envelopes to both control and intervention groups.

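### The Wilcoxon signed-rank test, a paired test, is assigned to change between two unmatched arms, and the plan does not say which test decides its between-arm hypotheses

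*Protocol article*

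**What the plan says.** Under Data Analysis, the protocol article assigns two tests to the outcomes over time. The first sentence reads: "The Wilcoxon Signed Rank test will be used to determine whether any changes in outcome variables occurred within and between groups over time". The next reads: "Mann-Whitney U test will be used to confirm whether there is an interaction between time and group". One threshold covers everything: "All analyses will be conducted using SPSS version 18 with a pre-defined level of statistical significance at p < 0.05".

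The design is two parallel groups (Methods/Design: "The pilot study using randomised controlled trial design (parallel-group trial"), allocated without matching (Randomisation: "Simple randomisation using a randomisation table (computerised sequence generation) will be used"). The Hypotheses section puts all its expectations as comparisons between arms: "Anticipated outcomes for the intervention group when compared to the control group receiving usual care will include", followed by higher scores for self-management, self-efficacy and knowledge. These correspond to the three primary outcomes under Data Collection. No sentence links a particular test to a particular hypothesis.

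**The concern.** A signed-rank test works on one difference per patient, here Time 2 minus Time 1. It has nothing to work on between arms, because no patient in one arm is paired with a patient in the other. Naming it for change between groups is therefore an error in what the plan states, and not a detail left to a fuller document.

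If run as the sentence suggests, it yields one before/after p-value in each arm. Neither answers a between-arm hypothesis, and setting the two side by side does not answer it either. Both arms may well change without any programme effect: Time 1 falls during a coronary care admission, Time 2 one month later, and usual care itself includes education and referral to a diabetes educator where needed. If both arms improve equally, chance alone will often make one p-value fall below 0.05 and the other not. With no deciding test named, that pattern could be reported as benefit and carried into the planning of the larger study.

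**Working it through.** **Does the test fit the purpose?** The signed-rank test needs paired or one-sample data. The arms are parallel and simply randomised, with no matching described, so no pairs exist across arms. Of the two roles in the first sentence, change within an arm is possible and change between arms is not.

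**Is a valid between-arm test present?** With two time points and two arms, a time-by-group interaction is the difference between arms in change from Time 1 to Time 2. Mann-Whitney U on the change scores tests this without pairing. The plan does not say that change scores are the variable.

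**Figures in the plan.** None is attached to the choice of test. The attrition step under Sample size reproduces: 10 / (1 − 0.20) = 12.5, rounded up to 13 per group.

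**What happens if the within-arm p-values are compared?**

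Inputs:
- Total of 30 in two groups and 20% attrition (Sample size). With an equal split, which is an assumption, 15 × 0.80 = 12 completers per arm.
- Significance level 0.05 (Data Analysis). The number of sides is not stated; two-sided is assumed.
- Normal change scores with the same true mean change in both arms, so there is no programme effect. The size of this common change, in SDs of the change score, is an assumption. The document gives none, so a range is shown.

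Formula: if p is the probability that the signed-rank test is significant in one arm, and the arms are independent with the same true change, then

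P(significant in intervention, not in control) = p × (1 − p).

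This is largest at p = 0.5, where it is 0.5 × 0.5 = 0.25. So 25% is a ceiling. The pattern is rarer when the common change is either very small or very large. Two checks against simulation at 12 per arm:
- Common change 0.5 SD: p = 0.304, so 0.304 × 0.696 = 0.212; simulated 0.207.
- Common change 0.7 SD: p = 0.552, so 0.552 × 0.448 = 0.247; simulated 0.242.

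Simulated results per outcome, 12 per arm, no programme effect:

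| Common change (SD) | Significant in intervention arm only |
|---|---|
| 0 | about 4% |
| 0.2 | about 8% |
| 0.4 | about 17% |
| 0.6 | about 25% |
| 0.8 | about 22% |
| 1.0 | about 12 to 13% |
| 1.2 | about 4.5% |

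Mann-Whitney U on change scores was significant in 4 to 5% of trials whatever the common change. With 10, 12, 13 or 15 per arm and common changes from 0 to 1.0 SD, it ranged from 3.8% to 5.2%. The misleading pattern together with a significant Mann-Whitney result occurred in only about 1 to 2% of trials.

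**The case against.** The strongest reply is that the plan already contains a sound between-arm test. The sentence on Mann-Whitney U follows directly, its natural reading is a test of change scores, and the word *confirm* may mean no more than *test*. If that result is respected, the excess of false signals disappears. This stands, and it limits the point: the plan does not lack a valid test. It assigns an invalid one to the same task and leaves open which of them decides.

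A reader might infer that the plan makes within-arm p-values the basis for judging the hypotheses. The documents do not support that, since no sentence gives them that role. Nor are the percentages above the plan's type I error. They are the frequency of a pattern that misleads only if the Mann-Whitney result is set aside.

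A reader might also blame the unequal arm sizes that simple randomisation tends to produce. That is not why the test fails: with exactly 15 per arm the patients would still be unmatched.

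Finally, this is a pilot aimed at feasibility and acceptability. That lowers the stakes but does not remove them. The article states comparative hypotheses, claims power of 0.9, sets a significance threshold and intends the results to guide the sample size of a larger study.

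**Conclusion.** The plan is wrong as written on one point and unclear on another. The signed-rank test cannot assess change between two independent arms. The test that can, Mann-Whitney U on change scores, is named without its variable and without being given the decision on the hypotheses.

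The room this leaves for misreading depends on how much both arms change for reasons other than the programme. Per outcome, at 12 per arm, the chance that only the intervention arm is significant runs from about 4% with no common change to a ceiling of 25% near 0.6 SD, and falls again for larger changes. This rests on normal change scores, equal arms, two-sided testing and no programme effect. That the signed-rank test does not fit the comparison rests on none of these assumptions.

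**What to change.** In the Data Analysis section:

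1. Delete the words *and between* from the sentence on the signed-rank test, and label that test as descriptive information on change within each arm that supports no conclusion about the programme.
2. State that Mann-Whitney U is applied to change scores (Time 2 minus Time 1), compared between arms.
3. State that each hypothesis on self-management, self-efficacy and knowledge is judged solely by that comparison. A Time 2 comparison adjusted for Time 1 is an acceptable alternative but is not needed to repair the plan.

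The cost is wording only: no additional patients, visits or data. What is given up is the use of within-arm p-values to support a claim of benefit.

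### The unadjusted Mann-Whitney comparison is valid on change scores but, unless the Time 1–Time 2 correlation is high, clearly less precise than adjusting each primary outcome for its Time 1 score

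*Protocol article*

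**What the plan says.** Under Measures, the three primary outcomes (self-care on the SDSCA, self-efficacy on the DMSES, knowledge on the DKQ) are each scored twice. For self-efficacy, for example: "Data will be collected at Time 1 and Time 2, and will be measured using the Diabetes Management Self-Efficacy Scale". The Procedure section places the baseline measurement before random assignment.

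The Data Analysis section chooses non-parametric tests because the sample is small. It opens with "Prior to undertaking statistical tests, the homogeneity of the sample will be examined" and applies chi-square and Mann-Whitney tests to disease and demographic variables. For the outcomes it names two tests. One is the Wilcoxon signed-rank test, for changes over time within and between groups. The other is the one at issue: "Mann-Whitney U test will be used to confirm whether there is an interaction between time and group". The signed-rank test is a paired procedure and cannot compare two independent groups, so the Mann-Whitney test carries the between-group comparison.

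On size and allocation: "A total of 30 patients for 2 groups will be required", and "Simple randomisation using a randomisation table (computerised sequence generation) will be used".

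**The concern.** A Mann-Whitney test takes no covariate. With two time points it addresses a time-by-group interaction only if it is applied to each patient's change (Time 2 minus Time 1). Subtraction uses the baseline score with a fixed weight of 1, whereas the efficient weight is the regression slope, which equals r when the two time points have equal SDs. If the test is applied to Time 2 scores instead, the weight is 0 and baseline is ignored. Either way, information already collected is partly wasted.

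This matters because the trial is small and does make comparative claims. The Hypotheses section predicts higher scores in the intervention group on all three outcomes, the Sample size section claims power of 0.9, and Data Analysis sets a 0.05 significance level. Simple randomisation does nothing to balance Time 1 scores between arms.

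**Working it through.** **Inputs from the article.** 30 patients in two groups; 20% attrition; significance level 0.05; simple randomisation.

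**Assumptions.** The article gives no r, SD or effect size. I take r from 0.3 to 0.8, an effect of 0.8 SD, equal arms of 15, equal SDs at both times, a two-sided test and, unless stated otherwise, normal data.

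**The plan's own figures.** Ten per group inflated for 20% loss is 10/(1 − 0.20) = 12.5, rounded to 13, which matches "Allowing 20% attrition rate, 13 patients per group will be required". The 10 itself cannot be reproduced, because no effect size or SD is given. By the two-sided normal formula it implies an effect of (1.96 + 1.28) × √(2/10) ≈ 1.45 SD. For the check I use 15 × 0.80 = 12 completers per arm.

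**Variance of the group contrast, relative to Time 2 scores alone (= 1).**
- Change score: 2(1 − r)
- ANCOVA on Time 1: 1 − r²
- Ratio of change to ANCOVA: 2(1 − r)/(1 − r²) = 2/(1 + r)

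| r | Change | ANCOVA | Ratio |
|---|---|---|---|
| 0.3 | 1.40 | 0.91 | 1.54 |
| 0.5 | 1.00 | 0.75 | 1.33 |
| 0.7 | 0.60 | 0.51 | 1.18 |
| 0.8 | 0.40 | 0.36 | 1.11 |

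The ratio exceeds 1 for every r below 1. Below r = 0.5 the change score has a larger variance than Time 2 scores alone.

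**Simulated power, 12 per arm, effect 0.8 SD.**

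| r | Mann-Whitney on change | ANCOVA | Quade's rank ANCOVA |
|---|---|---|---|
| 0.3 | 32% | 48% | 46% |
| 0.5 | 42% | 55% | 51% |
| 0.7 | 63% | 72% | 66% |
| 0.8 | 81% | 86% | 79% |

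Mann-Whitney on Time 2 scores alone has about 42% at r = 0.3, 0.5 and 0.7. Type I error was near 5% for all methods. The ANCOVA column is parametric, so part of its lead over Mann-Whitney comes from not using ranks. The rank-based remedy gains about 14, 9 and 3 points at r = 0.3, 0.5 and 0.7, and nothing at 0.8.

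**A bounded, discrete score.** With outcomes rounded to a 0–8 scale, as for the DKQ, Mann-Whitney on change against ANCOVA gave 30% against 48%, 38% against 54%, and 57% against 69% at r = 0.3, 0.5 and 0.7.

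**A very large effect.** At 1.45 SD with 12 per arm, the same comparison gave 79% against 93%, about 91% against 97%, and 99% against nearly 100%. The loss matters less if the effect is that large and r is high.

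**Chance imbalance.** At 15 per arm the baseline difference has SE √(2/15) = 0.365 SD, so P(difference above 0.5 SD in either direction) = 2[1 − Φ(0.5/0.365)] = 2[1 − Φ(1.37)] ≈ 17% for any one outcome. Given a 0.5 SD imbalance, the expected Time 2 contrast shifts by 0.5r SD and the change contrast by −0.5(1 − r) SD. At r = 0.5 these are +0.25 and −0.25 SD. ANCOVA removes the expected shift.

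**The case against.** The best defence is that a change-score comparison is legitimate. It uses the Time 1 score, is unbiased over randomisation, and holds its type I error. That stands. A reader might infer that the plan ignores baseline, or that its test is invalid; the text does not support either, since the interaction wording points to change scores.

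A reader might also infer that the plan counts on its homogeneity check to deal with imbalance in the outcome scores. The article does not say so: the tests it names for that step cover disease and demographic variables, not Time 1 outcome scores. What follows that check, and whether estimates and intervals will be reported, are details an article may leave to a fuller document. They are no part of this point.

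It can be said, too, that small samples call for rank methods. That is reasonable, but it does not exclude adjustment: Quade's test is rank-based, and a permutation p-value does not depend on normality. It remains true that Quade's test has no advantage over the change-score test when r is about 0.8.

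Finally, this is a feasibility pilot, and the SDs and correlation needed for a larger trial can be taken from the same data whichever test is used. That limits the consequence. It does not remove it, because the article itself states comparative hypotheses and a power claim.

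**Conclusion.** The point holds as one of efficiency. The article fixes an unadjusted between-group test although valid baseline covariates are available for all three primary outcomes. Against ANCOVA, the change-score test gives up about 16 percentage points of power at r = 0.3, 13 at 0.5, 9 at 0.7 and 5 at 0.8, some of which is the cost of ranks. In addition, a baseline difference above 0.5 SD will arise by chance in about one trial in six for a given outcome, and neither version of the Mann-Whitney test corrects for it.

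These sizes rest on an assumed effect of 0.8 SD, 12 completers in each of two equal arms, equal SDs, and mostly normal data. Since the article gives no r, the loss could be small if the scores are highly stable over one month. That the change-score variance exceeds the adjusted variance for every r below 1 does not depend on the assumed effect or sample size.

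**What to change.** In Data Analysis, replace the Mann-Whitney interaction test. For each of SDSCA, DMSES and DKQ, pre-specify an ANCOVA of the Time 2 score on group and the Time 1 score, and report the adjusted difference with its 95% CI. Because the sample is small, take the p-value from a permutation of group labels. Give Quade's rank ANCOVA as a sensitivity analysis.

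The cost is one degree of freedom (21 instead of 22 residual degrees of freedom with 24 completers) and slightly more analysis work. No extra patients, visits or measurements are needed.
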